Some of the above examinations will be performed a total of three times: at the start of the study, after 3 months, and after 6 months. Periodontal treatment will be completed by 2 months from the start of the study. Oral hygiene instruction will be provided to both groups at the start of the study, after 3 months, and after 6 months. In cases where there is a change in diabetes treatment during the study period, the details will be recorded.

(3) Planned duration of subject participation

Six months.

(4) Usage, dosage and administration period of study drugs

Not applicable.

(5) Study drug dosage form/content, properties, packaging, labeling, and storage

Not applicable.

(6) Provisions regarding concomitant medication (therapy)

Not applicable.

(7) Drug withdrawal method

Not applicable.

(8) Management and delivery procedures for study drugs

Not applicable.

(9) Drug administration guidance information

Not applicable.

(10) Case enrollment, allocation

Subject enrollment:

The principal investigator or a co-investigator will: 1) obtain written consent; 2) write the date on which consent was obtained and the items needed to link the subjects to the subject identification code on the subject identification code list kept by the principal investigator; 3) submit the case report form using the subject identification code to the study office (medical office for the Department of Preventive Dentistry); and 4) report immediately in the event of consent withdrawal, discontinuation, or dropout.

Subject allocation:

The subjects will be allocated to the treatment groups with a table of random numbers. Using a stratified block randomization allocation method, adjustments will be made according to baseline serum HbA1c (≥8% and <8%), whether a patient is receiving insulin treatment, and types and number of drugs (≤2 or ≥3) a patient is taking.

(11) Handling at completion of study

After the completion of the study, the principal investigator will provide the treatment he considers to be the most appropriate for each subject, including treatment based on the findings obtained in this study.

7. Assessments

(1) Primary endpoint

Serum HbA1c (National Glycohemoglobin Standardization Program [NGSP] value)

(2) Secondary endpoints

Periodontal status (number of teeth present, probing pocket depth, clinical attachment level, bleeding on probing, Plaque Control Record)

Hematological index (glycated albumin)

Blood biochemical index (oxidative stress balance)

QOL

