When a decision is made to discontinue or cease the study, a report to that effect together with the reason will be made in writing to the Hospital Director without delay.

13. Study period

From March 1, 2014 to March 31, 2016.

14. Data aggregation and statistical analysis

Data analysis will be conducted from the following observations:

1) Role of plaque control instruction in type 2 diabetes patients: The significance of plaque control instruction will be investigated from a comparison between the start of the study and the time of reassessment in the oral hygiene instruction group, including its effect on QOL.

2) Significance of periodontal treatment: The effects of periodontal treatment in type 2 diabetes patients will be discerned from a comparison of the oral hygiene instruction group and the non-surgical periodontal treatment group.

15. Target patient number and rationale

The target patient number is 20 for each group (40 patients total).

The number of patients is calculated to be 20 based on analysis of the serum HbA1c level in a previous study (see reference) on periodontal treatment in diabetes patients. To determine the sample size when the *t*-test is used, calculations were performed using SPSS Samplepower (IBM, Tokyo, Japan). Under the conditions of α=0.05 and β=0.20, with a two-tailed *t*-test, the predicted HbA1c level was 7.31% in the oral hygiene instruction group and 6.51% in the non-surgical periodontal treatment group. With an assumed standard deviation of 0.8, significance was hypothesized when the mean serum HbA1c differed by 0.8% as a result of periodontal treatment. As a result, 17 patients are needed for the study. Assuming a 15% dropout rate, the number is set at 20 patients.

16. Subjects’ rights, safety, and disadvantage

(1) Human rights (protection of privacy)

Subject data are coded and test results are provided to the person conducting the analysis at Okayama University so that individual subjects cannot be identified. To combine the data from the examination table, questionnaire, and each test, the same symbols are given to the same subject being examined. After the study has been completed, these data will be destroyed.

(2) Patient safety, disadvantage

Health insurance and other measures needed to compensate for health damage to subjects are not adopted.

Reason: There is the possibility only of slight pain when blood is taken. No damage to health is foreseen.

17. Cost to patients

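### "Types" of drugs is named as a stratifier without levels; taken literally it over-stratifies 40 patients, and the only test named ignores the stratifiers and baseline HbA1c

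*Protocol*

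**What the plan says.** Section 6(10), under subject allocation, sets the method: "Using a stratified block randomization allocation method". Three factors are listed: baseline HbA1c in two bands split at 8%, "whether a patient is receiving insulin treatment", and "types and number of drugs (≤2 or ≥3) a patient is taking". For the third factor only the count has levels (two or fewer, three or more). No block size is given. Section 6(2) adds that one member of the research group allocates from a table of random numbers.

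Section 15 sets the size: "The target patient number is 20 for each group (40 patients total"). It rests on a two-sided t-test "Under the conditions of α=0.05 and β=0.20", with predicted HbA1c of 7.31% and 6.51%, SD 0.8, 17 patients needed and 15% dropout. Section 14 describes the effect of treatment as coming from a "comparison of the oral hygiene instruction group and the non-surgical periodontal treatment group" and names no model.

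**The concern.** A block list can be drawn up only when every stratifier has defined levels. As worded, whoever prepares the list must decide what types means. One choice is harmless: treat the phrase as a single count factor. The other multiplies the cells until most hold one or two patients, and an incomplete block does little to hold the arms level. The balance lost would be on HbA1c, which is the primary endpoint, and on insulin use. This is a rule for allocation, so it has to be settled before the first patient is randomised and cannot wait for an analysis plan.

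The second strand is linked. The design goes to the trouble of stratifying on strong predictors of outcome, but the one test it names, a two-sample t-test, does not use them. In a trial of this size, baseline HbA1c is the cheapest available source of precision.

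**Working it through.** **1. The plan's own sample size.** Inputs from section 15: difference 7.31 − 6.51 = 0.80, SD 0.8, α = 0.05 two-sided, β = 0.20. The noncentral t gives power of 78.1% at 16 per group and 80.7% at 17, so 17 per group. Dropout: 17 / (1 − 0.15) = 20 per group, 40 in total. The stated figures reproduce.

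**2. Number of cells.** The stated levels give 2 × 2 × 2 = 8 cells; 40 / 8 = 5 patients per cell. If types has k categories there are 8k cells. Assuming k = 3: 24 cells, 40 / 24 = 1.7 each. Assuming k = 4: 32 cells, 40 / 32 = 1.25 each. The protocol gives no k.

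**3. Unfilled blocks.** Simulation of 40 patients, permuted blocks within cells, equally likely cells. Block size is an assumption. Share of started blocks left unfilled:

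| Cells | Blocks of 2 | Blocks of 4 |
|---|---|---|
| 8 | 18% | 46% |
| 24 | 45% | 90% |
| 32 | 54% | 95% |

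With uneven cells (assumed: HbA1c of 8% or more in 19–37% of patients, insulin 30%, three or more drugs 40%), 24 to 32 cells with blocks of 4 leave about 78–91% unfilled, and 8 cells about 45–46%.

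**4. Balance on the factors.** Same uneven assumptions, blocks of 4. Chance that the arms differ by 4 or more patients within the subgroup:

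| Subgroup | 8 cells | 24–32 cells | Simple randomisation |
|---|---|---|---|
| HbA1c 8% or more | 4–6% | about 15–26% | 19–37% |
| On insulin | 4–6% | about 18–24% | about 31% |

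So 8 cells protect both factors well, and 24 to 32 cells give back much of that protection. Smaller blocks soften the loss. At 8 cells with blocks of 2 the corresponding chance is about 1% or less, though such blocks are more predictable.

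**5. Cost of unequal arms.** t-test power at the plan's effect is 86.9% at 20/20, 86.6% at 22/18 and 85.5% at 24/16.

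**6. Gain from ANCOVA.** With baseline–outcome correlation ρ, the residual SD is 0.8 × √(1 − ρ²). The noncentrality is 0.8 / (residual SD × √(2/17)), with √(2/17) = 0.343. ρ is an assumption, because the protocol gives none.

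| ρ | Residual SD | Noncentrality | Power, 17 per group |
|---|---|---|---|
| 0 (t-test) | 0.800 | 2.92 | 80.7% |
| 0.3 | 0.763 | 3.06 | 84% |
| 0.5 | 0.693 | 3.37 | 90% |
| 0.7 | 0.571 | 4.08 | 98% |

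These use 32 degrees of freedom. Three covariates leave 34 − 5 = 29, which changes each figure by about 0.2 points or less. Residual covariate imbalance costs a little more. Simulating 34 completers under 8-cell blocks of 4, with insulin and drug number assumed to add nothing beyond baseline, gives about 83%, 89% and 97%. In the extreme case of ρ = 0 the adjusted analysis has about 78%, against 80% for the t-test.

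**The case against.** The strongest reply is that the only levels printed for the third factor are two or fewer and three or more, so the natural reading is a single count factor and 8 cells. On that reading the scheme works. This largely stands: the 24 to 32 cells are an assumption about an undefined word. What remains is that the word is there and has no levels.

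A reader might also infer several stronger points that the documents do not support.

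- **That most blocks stay unfilled.** With 8 cells this is false for blocks of 2 (18%) and of 4 (46%). It becomes true with blocks of 6 (68%) or more cells, and the protocol fixes neither. An unstated block size is not itself a defect.
- **That 20 per group will not be delivered.** Section 15's 20 is a recruitment target built from 17 plus dropout, not a promise of exact equality. With 8 cells and blocks of 4 the mean arm difference is about 2 patients, against 5 under simple randomisation, and 22/18 costs about 0.3 points of power.
- **That only 8 of 40 patients will have HbA1c of 8% or more.** This takes 7.31% as a baseline mean: 1 − Φ((8 − 7.31)/0.8) = 19%. In section 15 that figure is the predicted level in the instruction group, an outcome. With SD 0.8, baseline means of 7.0, 7.5 and 8.0 would give 11%, 27% and 50%.
- **That minimisation is required.** Against 8 cells with blocks of 4 it evens out arm size but gives about the same factor balance, at the price of a running tally. It is a trade-off.

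Finally, choosing a model is ordinary SAP work, section 14 fixes none, and section 15 names the t-test for sizing only. That also stands: the missing model is not a fault. The ANCOVA is a recommended improvement on the one test the protocol names.

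**Conclusion.** The point holds in a limited form and is minor. The allocation rule names a stratifier without levels, so it cannot be carried out as written without someone interpreting it. The 8-cell reading is sound. The literal reading with 3 or 4 drug types would raise the chance of a difference of 4 or more among patients with high HbA1c from 4–6% to about 15–26%, close to what simple randomisation gives. Those figures rest on assumed prevalences, an assumed number of types and blocks of 4.

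The loss would be in balance and credibility, since the direct power cost of unequal arms is under 1.5 points even at 24/16. The larger gain is in the analysis. Adjusting for baseline HbA1c and the stratifiers adds roughly 3 to 17 points of power for ρ from 0.3 to 0.7 (before the small cost of the covariates), on the plan's own effect and SD. If ρ were close to zero there would be no gain and a loss of about 2 points.

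**What to change.** 1. In section 6(10), delete the words that bring types into the third factor, leaving number of drugs (two or fewer, three or more). Keep stratified blocks with the resulting 8 cells. This costs one line of protocol text, approved by the Ethics Committee before the allocation list is made. Balance on drug class is given up as a design feature; class can still be reported at baseline.

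2. In section 14, or in the SAP if one exists, state the primary between-group comparison as an ANCOVA of HbA1c at the 6-month examination on group, with continuous baseline HbA1c, insulin use (yes/no) and number of drugs (two or fewer/three or more) as covariates. No new data are needed, because all three are recorded in order to allocate. The cost is three degrees of freedom and the small loss shown above if the covariates prove uninformative. The target of 20 per group can stay.

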**S2 Protocol. Protocol (in English).**

Clinical study protocol

Clinical study title: Comparison of the effects of oral hygiene instruction and periodontal treatment in patients with type 2 diabetes mellitus
（Comparison of the effects of oral hygiene instruction and periodontal treatment on patients with type 2 diabetes mellitus）

Principal investigator: [name]

Department of Preventive Dentistry, Okayama University Graduate School of Medicine, Dentistry and Pharmaceutical Sciences, Okayama, Japan

[name]

Telephone no. (ext.): [contact] [name]

[contact]

E-mail: [contact]

Emergency contact (medical office number): [contact]

Planned duration of study: March 1, 2014 – March 31, 2016.

Comparison of the effects of oral hygiene instruction and periodontal treatment in

patients with type 2 diabetes mellitus

Study protocol

1. Background

The “Basic Matters Related to Dental and Oral Health Promotion” are based on the “Dental and Oral Health Promotion Law” enacted in August 2012. It describes the relationship between oral status and general health, between dental diseases and lifestyle habits, and between oral health and medical expenses, as well as the promotion of research on prevention and treatment methods that are effective from their relation to dentistry. Innovation is needed especially in dental-medical collaborative model projects for diabetes patients, as the close relationship between periodontal disease and diabetes continues to be elucidated.

2. Study objectives and necessity

In this study, type 2 diabetes patients being treated on an outpatient basis at Okayama University Hospital will be divided into two groups, an oral hygiene health instruction group (given guidance on plaque control only) and a non-surgical periodontal treatment group (given guidance on plaque control and periodontal treatment). The purpose of this study is to compare the results of tests (clinical and blood biochemistry tests) performed 6 months after the conclusion of periodontal treatment (including full mouth scaling and root planing), and the effects on changes in quality of life (QOL) in these two groups.

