The current status of medical-dental collaboration for diabetes patients consists mainly of cooperation between medical and dental institutions by referring patients to each other, and the clinical significance is unclear. The results of this study will give clinical significance to the content of such collaboration (providing support for the improvement in diabetes status from periodontal treatment). This is promising for use as evidence for the introduction of periodontal treatment into health care services covered by health insurance, such as “Dental support additions to diabetes and other patients (provisional)” in future Health, Labour and Welfare administrations.

3. Summary of pharmaceuticals and medical equipment

Not applicable.

4. Subjects

(1) Inclusion criteria:

Patients who meet all of the following criteria will be included as subjects:

1. Currently receiving treatment for type 2 diabetes
2. Capable of participating in the study for 6 months
3. Supported by medical insurance
4. 30 years or older at the onset of study (at the time of informed consent)
5. Consenting patients (Patients who voluntarily provide written consent after receiving a full explanation and fully understanding participation in the study)
6. Outpatients

(2) Exclusion criteria:

Patients who are incompatible for any of the following reasons will be excluded:

- - - - 1. Undergoing dental treatment
        2. Pregnant or possibility of being pregnant
        3. Determined as unsuitable subjects (Other patients judged by the principal investigator or a co-investigator to be unsuitable as subjects)

5. Explanation of study to subjects and obtaining consent

Patients will be given an informed consent form approved by the Ethics Committee, Okayama University Graduate School of Medicine, Dentistry and Pharmaceutical Sciences and Okayama University Hospital, and the study will be fully explained both orally and in writing. Written consent will then be obtained at the discretion of the patients. In the event of a change in the protocol or other matters that may affect consent, such information will be provided to patients promptly and the decision on whether to participate in the study will be confirmed again. At the same time, the informed consent form or other relevant forms will be revised with advance approval by the same Ethics Committee, and consent will again be obtained from patients.

6. Study methods

The following are provided:

(1) Study type/design

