Randomized controlled study

(2) Study outline

| **Assessment**  • Primary endpoint: HbA1c  • Secondary endpoints: periodontal status, blood sugar, oxidative stress, and QOL  **Oral hygiene instruction group**  Receives oral hygiene instruction  Recruitment of study participants  **Non-surgical periodontal treatment group**  Receives oral hygiene instruction + scaling and root planning, professional toothbrushing and mechanical tooth cleaning |
| --- |

Figure. Study flow chart

Type 2 diabetes patients in the Nephrology, Diabetology and Endocrinology Department of Okayama University Hospital who consent to participate in the study will be introduced to the Department of Preventative Dentistry outpatient clinic. One member of the research group will separate patients into two groups, the oral hygiene instruction group and the non-surgical periodontal treatment group, using a table of random numbers (the patients will be asked not to inform the examiners of the group to which they are assigned). Thereafter, two dentists blinded to the group assignments will conduct periodontal examinations. Other dentists will then be in charge of oral hygiene instruction and periodontal treatment. For the periodontal examination, calibration will be repeated in advance until the kappa value (a reliability assessment index) exceeds 0.8 for inter- and intra-operator agreement.

The periodontal examination includes probing pocket depth, clinical attachment level (distance from the border between the tooth crown and root to the bottom of the periodontal pocket), bleeding on probing (whether bleeding is seen when the periodontal pocket depth is measured), and the degree of plaque buildup.

Blood tests are routinely conducted as part of regular medical examination in the Nephrology, Diabetology and Endocrinology Department (and will be arranged so that examinations are conducted in the Nephrology, Diabetology and Endocrinology Department and the Department of Preventive Dentistry on the same day). In blood tests, glycated hemoglobin (HbA1c) and glycated albumin will be assessed. Remnant blood from examinations (blood that would otherwise be disposed of as medical waste) will be used by the research group for measurement of the oxidative stress balance.

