
(3) Safety assessment

Not applicable.

8. Observation and test items

(1) Patient characteristics: Chart number, patient’s initials, sex, date of birth, race, inpatient or outpatient, height, weight, complications, past medical history, history of present illness, previous treatment, and other.

(2) Confirmation of subjective and objective symptoms: Confirmation by interview (with reference to the symptom diary if available).

(3) Blood test: Same test items as in regular medical examination.

(4) Blood biochemistry test: Same test items as in regular medical examination. Factors associated with oxidative stress will also be assessed to confirm the relationship between oral health and whole body status.

(5) Periodontal examination: Number of teeth present, probing pocket depth, clinical attachment level, bleeding on probing, and Plaque Control Record.

(6) Questionnaire survey on QOL.

Table. Study Schedule

| Item | | Study initiation | Period of periodontal treatment | Observation period | |
| --- | --- | --- | --- | --- | --- |
| Timing | | Week 0 | Less than 2 months | After 3 months | After 6 months |
| Examination | | Examination 1 | Examination 2–5 | Examination 6 | Examination 7 |
| Consent obtained | |  |  |  |  |
| Confirmation of patient characteristicsa | |  |  |  |  |
| Oral hygiene instruction | |  |  |  |  |
| Periodontal treatment | |  |  |  |  |
| Confirmation of subjective and objective symptoms | |  |  |  |  |
| Questionnaire survey on QOL | |  |  |  |  |
| Clinical tests | Blood testsb |  |  |  |  |
| Blood biochemistry  testsc |  |  |  |  |
| Periodontal examination | |  |  |  |  |

Open circles () indicate measures that will be performed prior to dental intervention. Black circles () indicate measures that will be performed after dental intervention.

aPatient characteristics indicate characteristics routinely noted in medical care, such as age, sex, past medical history, and complications.

bBlood tests indicate the same tests performed during regular medical examination.

cBlood biochemistry tests indicate the same tests performed during regular medical examination. In addition, factors associated with oxidative stress will be assessed to confirm the relationship between oral health and whole body status.

9. Discontinuation criteria

- 1. A subject asks to stop participating in the study or withdraws consent.
  2. It is found after enrollment that eligibility requirements are not fulfilled.

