  3. Continuation in the study is difficult due to exacerbation of complications.
  4. A subject is discovered to be pregnant.
  5. The entire study is discontinued.
  6. Dental treatment is found to be necessary for a subject in the oral hygiene instruction group after assignment.
  7. A physician determines that discontinuation is advisable for some other reason.

10. Handling when an adverse event occurs

(1) Response to patients when an adverse event occurs

When an adverse event that requires treatment occurs in a subject, the subject will be notified and appropriate medical care for the adverse event will be provided.

(2) Report of a serious adverse event

If a serious adverse event occurs or there is concern of such an event occurring, a report will be made immediately to the Hospital Director of Okayama University Hospital.

11. Report of deviation from protocol

The following matters are provided in accordance with GCP:

- The principal investigator and co-investigators will not deviate from or make changes to the study protocol before obtaining approval from the Hospital Director based on advance review of the Ethics Committee.
- The principal investigator and co-investigators may deviate from or change the study protocol before obtaining advance approval from the Ethics Committee for compelling reasons in order to avoid an emergency. In such cases, the principal investigator or a co-investigator will submit the details regarding the deviation or change and the associated reasons, together with a proposal for revision of the study protocol if necessary, to the Ethics Committee without delay, and approval from the Ethics Committee and Hospital Director will be obtained.
- In cases of deviation from the study protocol, the principal investigator or a co-investigator will record all items of deviation and the reasons for them.

12. Completion, discontinuation, or cessation of study

(1) Study completion

At the completion of the study, the principal investigator will submit a study completion report to the Hospital Director without delay.

(2) Study discontinuation or cessation

The principal investigator will consider whether or not to continue the study in the event of either of the following:

1) Recruiting subjects is difficult and reaching the planned number of subjects is judged to be unlikely.

2) The Ethics Committee asks for changes to be made in the protocol or other matters, and those changes are judged to be difficult to make.

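### Section 9 item 6 discontinues, after randomisation and in the oral hygiene instruction arm only, subjects found to need an undefined dental treatment, and the protocol makes no provision for their 3- and 6-month HbA1c

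*Protocol*

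**What the plan says.** Section 9 of the protocol lists seven discontinuation criteria. Item 6 reads "Dental treatment is found to be necessary for a subject in the oral hygiene instruction group after assignment". No matching item exists for the non-surgical periodontal treatment group. Neither item 6 nor exclusion criterion 1 in section 4(2), which uses the same term, says which dental treatment is meant. Item 6 also names no threshold and no one to decide.

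Other parts of the protocol bear on how item 6 should be read:

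- Section 6(11), on handling at study completion: "After the completion of the study, the principal investigator will provide the treatment he considers to be the most appropriate for each subject".
- Section 6(10), the enrolment steps: study staff must "report immediately in the event of consent withdrawal, discontinuation, or dropout". This is the only procedure attached to a subject's discontinuation.
- Section 9, item 1: "A subject asks to stop participating in the study or withdraws consent". Item 3: "Continuation in the study is difficult due to exacerbation of complications". Both speak of leaving the study, not only the regimen.
- Section 6(2): "Blood tests are routinely conducted as part of regular medical examination in the Nephrology, Diabetology and Endocrinology Department". HbA1c, the primary endpoint, comes from these tests, and the examination times are 0, 3 and 6 months. The same section places the periodontal examination after allocation.

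Sections 6, 8, 9 and 14, where a rule on HbA1c after discontinuation would belong, contain none.

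**The concern.** Randomisation makes the arms comparable at assignment. A rule that acts later, in one arm only, and on a condition that may be linked to the outcome can undo that. The inclusion criteria in section 4 require no dental examination, so a need for treatment can first come to light after allocation. The same finding then discontinues a control, while no corresponding rule applies to a treated subject.

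The protocol gives a reason to think the trigger may be related to the outcome: its background section says that "the close relationship between periodontal disease and diabetes continues to be elucidated". If the controls who leave differ in HbA1c from those who stay, the between-group comparison of section 14 is biased. If they do not differ, the trial loses only precision.

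An analysis plan can say which subjects are analysed, but it cannot supply study-time values that were not obtained. Whether those values are obtained is a matter for the protocol.

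**Working it through.** **1. The plan's own figure.** Inputs from section 15: means 7.31 and 6.51 (difference 0.80), SD 0.8, two-sided alpha 0.05, power 80%, 15% dropout, 20 per arm. The exact two-sample t-test (noncentral t) needs 16.7, hence 17 per arm, with power 80.7%. Allowing for dropout, 17/0.85 = 20. The stated size reproduces. With all 20 per arm observed, power is 86.9%.

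**2. Model for loss of controls.** Let f be the fraction of controls lost through item 6, and g the mean HbA1c of those lost minus that of those remaining. The full control mean equals the remaining mean plus f × g, so the observed difference is 0.8 − f × g. The standard error is 0.8 × √(1/20 + 1/n_c), where n_c = 20(1 − f). The protocol gives neither f nor g; both are assumptions. I cap f at 15%, its only attrition figure, and take g as 0, 0.3 or −0.3.

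| Controls lost | g | Shift f × g | Observed difference | Power | Type I error |
|---|---|---|---|---|---|
| 1 of 20 | 0.3 | 0.015 | 0.785 | 84.7% | 5.0% |
| 2 of 20 | 0.3 | 0.030 | 0.770 | 82.2% | 5.1% |
| 3 of 20 | 0.3 | 0.045 | 0.755 | 79.4% | 5.3% |
| 3 of 20 | 0 | 0 | 0.800 | 83.8% | 5.0% |
| 3 of 20 | −0.3 | −0.045 | 0.845 | 87.6% | 5.3% |

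At 3 lost, the standard error is 0.8 × √(1/20 + 1/17) = 0.264. The shift of 0.045 is 0.045/0.264 = 0.17 standard errors, or 0.045/0.8 = 6% of the planned difference. Type I error is the rejection rate when the true difference is 0 and the shift remains; it depends only on the size of the shift, not its sign.

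**3. Losses inside the dropout allowance.** If item 6 accounts for the whole 15% in controls and 3 treated subjects leave at random, 17 face 17. Power is 80.7% at g = 0 and 76.1% at g = 0.3, the latter with type I error 5.3%.

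**4. Keeping these controls in.** All 20 per arm are observed. If the care they receive had the full planned effect of 0.8, the difference would be 0.8(1 − f). This is an upper bound on dilution.

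| f | Difference | Power |
|---|---|---|
| 5% | 0.76 | 83.3% |
| 10% | 0.72 | 79.2% |
| 15% | 0.68 | 74.5% |
| 20% | 0.64 | 69.3% |

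If the care had half that effect (0.4), f = 15% would give 0.8 − 0.15 × 0.4 = 0.74 and power 81.3%. If it had none, power stays at 86.9%.

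**The case against.** The strongest case against is that this is a sensible rescue rule on which the protocol is merely silent. Five points support it.

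- **Discontinuation need not end follow-up.** Section 6(10) names withdrawal of consent, discontinuation and dropout as separate events. This stands: the text does not say that an item-6 subject leaves follow-up. Items 1 and 3 point that way without settling it.
- **HbA1c may be in the chart anyway.** It comes from routine tests, and the patient stays in diabetes care. This also stands in part, although nothing ensures values near 3 and 6 months or their use.
- **The trigger may have little to do with HbA1c.** A reader might infer that item 6 takes out every control with periodontal disease. The documents do not support that: controls go without periodontal treatment by design, and section 6(11) suggests that such care waits until completion. Care that cannot wait, or other dental care, is the more coherent reading. The item then applies less often, and the background statement on periodontal disease supports a weaker link.
- **Other rules apply to both arms.** Exclusion criterion 3 covers patients "judged by the principal investigator or a co-investigator to be unsuitable as subjects", and item 7 leaves discontinuation to a physician. Both are discretionary; they soften the asymmetry without removing it.
- **Removal keeps the contrast clean, and retention dilutes it.** At f = 15% the upper bound on dilution gives 75% power, against 79% under removal with g = 0.3. So the gain from retention is not power. This objection concerns how the values are analysed, not whether to obtain them.

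**Conclusion.** The point holds as a minor one. Item 6 is arm-specific, acts after randomisation, rests on an undefined term, and comes with no provision for later HbA1c. Followed as study exit, it can deplete the control arm selectively.

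The likely size is small. Even with 3 of 20 controls lost and an assumed gap of 0.3, the shift is 0.045, type I error 5.3% and power 79%. With one or two lost, type I error is 5.0% to 5.1% and power 82% to 85%. These figures rest on assumed f and g.

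A reader might go further and conclude that the trial is biased against periodontal treatment, or biased substantially. The protocol supports neither. It does not fix the sign of g: a positive gap shrinks the difference and a negative one inflates it. Larger effects need more losses than the 15% allowance, or a stronger link between dental need and HbA1c than anything in the document justifies. If there is no link, the only cost is precision.

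**What to change.** Reword section 9, item 6 along these lines: *A subject in the oral hygiene instruction group who needs dental care that cannot wait until study completion receives it and stops the allocated regimen, but remains in the study. The treatment and its date are recorded, and HbA1c at 3 and 6 months is still obtained from the routine clinic blood tests.* The main comparison can then be made as randomised, free of selection through item 6.

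The cost is one reworded item, with the ethics committee approval that section 26 requires, and almost no extra burden, since the blood tests take place anyway. The downside is the dilution shown above if the care lowers HbA1c. Collecting the values closes off no analysis: one that sets aside HbA1c measured after such treatment remains available as a sensitivity analysis.
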